## Abstract

**Background:**

There is an increasing need for Mental Health Promotion (MHP) among adolescents, especially in developing countries with limited resources and rapid socio-demographic transition. With the growing burden of mental health problems among adolescents (suicide, depression) and their preferences to seek help from their peers, improving Mental Health Literacy (MHL) and behaviours for First Aid in Mental Health (MH-FA) becomes crucial to promote their mental health.

**Methods:**

Schools are ideal settings for reaching the vulnerable adolescents. The proposed study evaluates the effectiveness of a classroom-based teacher-led integrated school mental health intervention called SUMS (MHP + MHL + MH-FA). The study will involve a pragmatic, cluster-randomised waitlist-controlled design to evaluate the effectiveness of SUMS intervention using schools as unit-of-randomisation. The study will be conducted in Srinivaspura taluka (Sub-district) of Kolar district (administrative unit of health) of Karnataka in collaboration with a multi-disciplinary expert team from NIMHANS (National Institute of Mental Health And Neuro Sciences), Bangalore-India and Department of Education, Government of Karnataka, India. A total of 8 schools (400 students studying in 6–8 grade) from Srinivaspura taluka will be randomised into intervention and waitlist control group. The intervention group will receive SUMS intervention through 10–15 h of classroom sessions. The primary outcome is the improvement in positive mental health literacy, as measured by the Mental Health-Promoting Knowledge (MHPK-10) scale. Changes in MH-FA knowledge and intentions, Mental health stigma, help-seeking and resilience are assessed as secondary outcomes. Data will be collected at baseline, 6-weeks, 6-months and 12-months post-intervention. The waitlist-control schools will receive the interventions at the end of the 12-month follow-up assessment in intervention-schools.

**Discussion:**

This is the first study to integrate Mental Health Literacy with Mental Health Promotion and behaviours for First Aid in Mental Health to promote mental health well-being among adolescent school children in India. With a need to build a more substantial evidence base on School Mental Health Promotion approaches in developing countries, the study findings will have implications for implementing and operationalising Health and Wellness Ambassador initiative in India.

**Trial registration:**

Clinical Trials Registry - India, CTRI/2019/07/020394. Registered prospectively on 29 July 2019. (ctri.nic.in/Clinicaltrials/pmaindet2.php?trialid=35724&EncHid=&userName=sums).

## Background

In recent years, there is an increasing concern about adolescents’ mental health, especially in developing countries. An estimated 10–20% of children and adolescents are affected by mental health problems worldwide [1]. Adolescence is a period that is characterised by rapid physical and psychological changes with altered social perceptions and expectations [2]. The expectations and the choices made during this period have a significant impact not only on current health-practices and well-being but also on their health as adults. We must engage with them and enable them to make right choices about their expectations and address their mental health needs effectively through mental health promotion (MHP). With rapid socio-demographic and lifestyle transition, such mental health promotion will help adolescents build resilience to cope well in difficult situations or adversities. This will be critical not only for their well-being during adolescence but also for their physical and mental health in adulthood.

Today, suicide is one of the leading cause of preventable deaths, and depression is one of the leading cause of morbidity among adolescents [3]. Based on the life-course perspective, it has been emphasised to target adolescents in school to accommodate the contextual factors that influence suicide during adolescence [4]. Even though these mental health problems have detrimental effects on well-being, and development in adolescence, a reluctance to seek professional help due to stigma and lack of mental health knowledge has been documented in various studies across the globe [5–7]. Thus, there is a need to improve help-seeking to reduce the growing burden of mental health problems among adolescents and promote mental health literacy as an important strategy to promote help-seeking among adolescents [8–10].

Mental health literacy (MHL) is defined as “knowledge and attitudes regarding mental health that aid in recognition, management and prevention of mental health issues” [11]. Low levels of MHL were associated with depression and MHL among adolescents was positively associated with their mental health [12, 13]. Even though mental health literacy has significant implications on adolescent mental health, poor mental health literacy has been demonstrated for adolescents across various settings [14, 15]. Thus, MHL must become a focus of mental health interventions for adolescents. With the adolescents preferring to disclose mental illness symptoms to their peers and reluctant to seek professional help, the importance of improving behaviours for First Aid in Mental Health (MH-FA) to facilitate social support and help-seeking for mental illness cannot be overlooked. Mental health first aid is the help provided to a person who is developing a mental health problem, experiencing a worsening of an existing mental health problem or in a mental health crisis [16]. As adolescents begin to make decisions about their health and often have a preference for seeking help from peers, mental health literacy to adolescents should be provided ideally as a part of the school curriculum and not as ad-hoc events that occur infrequently (such as mental health parades, campaigns etc.,) [8]. It is further emphasised that schools should promote not only positive mental health but also MHL to enable students to understand mental health problems, reduce mental health stigma, promote mental health self-care and help-seeking behaviours of students [13]. Thus, integration of First Aid in Mental Health (MH-FA) with MHP and MHL, becomes a potential strategy for mental health promotion and prevention in adolescents.

Given the critical role of education in health literacy, schools become an ideal setting for reaching vulnerable adolescents for improving mental health literacy. This is because adolescents spend most of their time in schools, and health is intrinsically linked with education. Furthermore, many risks and protective factors for adverse mental health outcomes are operated in the school context. Presently, the evidence base for educational interventions targeting adolescents for mental health literacy and mental health promotion is limited [17]. Even though there is a concept of Health Promoting Schools (HPS) by World Health Organization that provides a broad framework for action, there is little evidence on schools’ ability to implement this approach. Existing evaluations of schools that had implemented HPS initiative have shown that mental health (despite being an important outcome of HPS initiative) was not addressed, apart from substance use [18, 19]. A clear need for well-controlled research in the area of mental health literacy and mental health promotion has been documented due to previous studies with small sample sizes, lack of follow-up, low response rates and potential contamination [20].

In India, adolescent mental health assumes a great relevance where adolescents aged 10–19 years constitute about 22% of the population [21]. With increasing enrolment in secondary schools in India, schools become the ideal platform for promoting positive mental health among adolescents. Even though there are Adolescence Education Programme and Rashtriya Kishor Swasthya Karyakram programme in India, it was evident that such programmes have either failed to account for the mental health needs of school communities or failed to measure the changes or values that are intended for the sustenance of mental health promotion [22, 23].

Developing personal skills for both students and teachers has been emphasised for successful mental health interventions [13] Among various approaches to address mental health literacy in schools, a natural approach builds on schools’ existing social ecologies such as curriculum presented by usual classroom teachers. Also, teacher-led approaches were found to facilitate the creation of a school-wide environment of acceptance and normalisation of mental illnesses as well as facilitate recognition and help-seeking in adolescents [8]. MHL delivered by external providers had limited value on the sustained and enhanced MHL capacity embedded into educational systems [13]. Further, MHL delivered by teachers was found to have positive mental health literacy outcomes across various settings and teacher delivered MHL curriculum found to have an advantage in normalising mental health knowledge as a part of education [13].

With this in the background, we developed a classroom-based teacher-led integrated school mental health intervention called SUMS (MHP + MHL + MH-FA) based on “School Friendly” mental health literacy approach and “School-Based Integrated Pathway to Care Model” developed by Kutcher et al. [24]. Like MHL approach, SUMS intervention is based on existing classroom friendly pedagogical approach that can be easily delivered in the current educational systems without extracurricular or outside-of-school inputs [13]. Basically, SUMS intervention focuses on curriculum resource approaches delivered by teachers (https://mhlcurriculum.org/) where a curriculum resource guide was developed through desk review and expert inputs. The curriculum resource guide contained content and delivery methods for each SUMS intervention (MHL, MHP and MH-FA). This curriculum resource guide was adapted to the local context through key informant interviews and intervention designing workshops conducted among school teachers, students, block education officers and subject experts.

In this context, we have undertaken a cluster randomised controlled trial to evaluate the effectiveness of SUMS (Scaling Up of Mental Health in Schools) intervention (an integrated school mental health intervention) for adolescents, integrated into the classroom and delivered by teachers. We hypothesise that SUMS intervention delivered by teachers will lead to significant improvement in mental health knowledge, positive attitudes toward mental illness, and behaviours for First Aid in Mental Health as compared to ongoing regular school approach among school-going adolescent children. The ongoing regular school approach was used as comparator to reflect real-life scenario.

### Objectives

This study’s primary objective is to assess the effectiveness of evidence-informed integrated school mental health intervention (SUMS) in promoting mental health knowledge, positive attitudes toward mental illness, and behaviours for First Aid in Mental Health among adolescent school children. Furthermore, we will explore SUMS intervention’s potential influence on a range of adolescent health-related outcomes such as academic achievement, absenteeism rate, educational stress, suicidal ideation, bullying, and substance use. Additionally, we will explore the implementation process of the intervention and identify contextual factors associated with outcomes.

## Methods

### Study design

The study will use a pragmatic, cluster randomised waitlist-controlled design with schools as unit-of-randomisation to evaluate the effectiveness of SUMS intervention. The study will follow consort guidelines for cluster randomised trial (Fig. 1).

**Fig. 1 Fig1:**
[figure not shown]
Trial Design. MHP: Mental Health Promotion. MHL: Mental Health Literacy. MH-FA: First Aid in Mental Health. * Data obtained from Department of Public Instruction Office, Kolar for the year 2016

### Study area

The study will be conducted in Srinivaspura taluka (Sub-district) of Kolar district (administrative unit of health) of Karnataka (https://kolar.nic.in/en/) in collaboration with a multi-disciplinary expert team from NIMHANS (National Institute of Mental Health And Neuro Sciences), Bangalore-India and Department of Education, Government of Karnataka, India. Kolar district is the Public Health Observatory for Department of Epidemiology, NIMHANS.

### Study setting

The Department of Education in Karnataka state has three levels of schools viz., Primary (1–5 grades), Higher-Primary (6–8 grades) and High-schools (9–10 grades). The study will be conducted in higher-primary public schools in Srinivaspura taluka of Kolar District, Karnataka. Higher-primary public schools usually include children from ages 13 to 15 years. These grades were chosen because this is the period where life skills curriculum were introduced and this period in the life span also represents the point of departure for the rapid increase in psychiatric diagnoses that occurs prior to age 25 years [24].

### Study subjects

The students from grades 6 and 7 will be included for the present study so that the students in grade-7 will have 12-month follow-up when they are in class-8.

### Inclusion criteria

All children enrolled in class 6th and 7th grade of the participating higher-primary public schools will be eligible for the present study.

### Exclusion criteria

(1) Children who did not give informed assent (2) Children whose parents/guardians did not provide written informed consent (3) Children who were absent for the baseline assessment even after two attempted visits (4) children aged> 15 years at enrolment.

### Intervention

**SUMS intervention (MHP + MHL + MH-FA)** is a classroom-based teacher-led integrated school mental health intervention that will promote positive mental health, mental health literacy and behaviours for First Aid in Mental Health among school-going adolescent school children. As described earlier, SUMS intervention takes the form of a classroom-ready resource (the curriculum resource guide) designed to be delivered by usual classroom teachers to students in grades 6 and 7 (ages 12 to 15 years). The curriculum resource guide contains 10 modules categorised under 3 units (Mental Health Promotion, Mental Health Literacy and First Aid in Mental Health). The ten modules are as follows: Positive mental health, Promoting Resilience, Promoting Mindfulness, Life Skills Education, Mental Health Literacy, Understanding Mental Health and Mental Illness, Stigma of Mental Illness, Information on specific mental illnesses, seeking help and finding support, First Aid in Mental health and strategy for mental health first Aid (Table 1). Each module’s purpose is to provide teachers with classroom-ready lesson plans, activities, and easily accessible resources. The ten modules are designed to be taught in sequence and are intended to be delivered on the usual school days through 10–15 h of classroom time.

**Table 1 Tab1:** SUMS Intervention-Curriculum framework

Units	Module	Teaching method
Mental Health Promotion (MHP)	Module 1: Positive mental health Module 2: Promoting Resilience Module 3: Promoting Mindfulness Module 4: Life Skills Education	Educational session followed by Participatory and experiential activities as recommended in the resource guide (Interactive discussions, Group discussion, Co-operative play, Storytelling. Role play, Brainstorming, Debate, within-school competitions, wall-magazine, etc.,)
Mental Health Literacy (MHL)	Module 5: Understanding Mental Health and Mental Illness Module 6: Stigma of Mental Illness Module 7: Information on specific mental illnesses Module 8: Seeking help and finding support	
First Aid in Mental Health (MH-FA)	Module 9: First Aid in Mental health Module 10: Strategy for First Aid in Mental health	

### Feasibility testing for SUMS interventions

The SUMS intervention curriculum resource guide will be translated into local language Kannada and will be piloted with concerned Block Education Officers for its clarity and suitability for training school teachers and students. Perceived intervention feasibility will be assessed by adapting a 4-item Feasibility of Intervention Measure (FIM). Any suggestions by Block Education Officers will be duly accommodated to improve the feasibility [25].

### Outcomes

The following core outcomes will be used to assess the intervention. All outcome measures will be measured at the individual student level.

#### Primary outcome

The primary outcome, **Positive mental health literacy** will be measured using a 10-item Mental Health-Promoting Knowledge (MHPK-10) scale. It is a valid and reliable one-dimensional instrument measuring knowledge of factors promoting good mental health among adolescents. The MHPK-10 had demonstrated good internal validity and test-retest reliability (r = 0.74) among adolescents. For each item, respondents rate items on 1–5 likert-type scale, the extent to which they are correct or wrong. The score range is 10–50, with a higher score indicating a higher positive mental health literacy [26].

#### Secondary outcomes

##### Mental health first aid knowledge and mental health literacy

This will be measured using a 35-item univariate scale, Mental Health Literacy Scale (MHLS). The scale will be adapted for use among adolescents. The score range is 35–160, with a higher score indicating a higher mental health literacy [27].

##### Personal and public stigma towards mental health among adolescents

This will be measured using the 24-item Peer Mental Health Stigmatization Scale (PMHSS). For the present study, the 8-item personal stigma subscale will be used. Τhe scale demonstrated adequate discriminant validity, internal consistency (α = 0.75) and test-retest reliability in adolescents [28].

##### Stigmatising behavior

 will be measured using the Reported and Intended Behaviour Scale (RIBS). Scores on the RIBS range from 4 to 20, with higher scores indicating more positive attitudes. The RIBS has a test-retest reliability of 0.75, and a Cronbach’s α of 0.86 [29].

##### Mental health help-seeking

This will be assessed using a 24-item Inventory of Attitudes towards Seeking Mental Health Services (IASMHS) scale. It consists of three subscales; Psychological Openness, Help-seeking Propensity, and Indifference to Stigma. The total help-seeking score is calculated as a sum of the subscale totals with higher scores indicate more favourable attitudes towards help-seeking [30].

##### Psychological distress

A 6-item self-administered **Kessler psychological distress scale (K6)** with good internal consistency (Cronbach’s alpha = 0.84) will be used. The total score ranges from 0 to 24 with a higher score indicating higher distress [31].

##### Resilience

A 25-item Connor-Davidson Resilience Scale (CD-RISC) will be used. The CD-RISC is a valuable measure to assess resilience among adolescents in low-income settings. Psychometric properties of the Kannada version of CD-RISC were established in a sample of adolescent girls from low-income settings. The total score ranges from 0 to 100, with higher scores reflecting greater resilience [32].

##### A semi-structured interview schedule

 will measure socio-demographic details and contain case vignettes/questions to assess MH-FA knowledge and intentions to provide MH-FA (proxy measures of behaviour change).

##### Exploratory outcomes

A compelling body of evidence points to the potential influence of SUMS intervention on a range of adolescent health-related outcomes such as academic achievement, absenteeism rate, educational stress, suicidal ideation, bullying and substance use, which will be explored.

##### Pre-testing of study instruments

The pre-validated study instruments will be translated into local language and back-translated for conceptual equivalence. For pre-testing, a sample size of 42 is estimated to establish reliability of at least 0.85, against acceptable value of 0.7 (with α = 0.05; β = 0.20) for a minimum of 6 items [33]. The translated study instruments will be pre-tested on a representative sample for cultural relevance and comprehensibility and validated for internal consistency before their final inclusion. The final study instrument administered will be bilingual.

##### Sample size and power

Positive mental health literacy measured using the 10-item Mental Health-Promoting Knowledge (MHPK-10) scale is considered primary outcome for the present study [26]. However, the Intra-Cluster Correlation for MHPK-10 score is unknown. Based on evidence from similar adolescents studies, we assumed a conservative and modest estimate of ICC (ρ) between 0.01 and 0.05 [34, 35]. From the Kolar District Report (as on 30/3/2016), an estimated average of 50 students is expected from grade-6 and 7 of each higher-primary schools. With a need for 4 schools per arm with 50 students per school, we powered the trial to be able to detect a standardised difference (difference in means/SD) of 0.37–0.56 (medium effect size) for MHPK-10 scores between intervention and control groups for a two-sided level of significance at 5% (*α* = 0.05) with 85% power. For the above assumption, the design effect varied from 1.5 to 3.5 for ICC (ρ) values from 0.01 to 0.05, respectively [36]. We expect a minimum sample size of 400 across 8 schools for 85% power. Even with a 5% loss to follow-up, the study will still have more than 80% power.

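### The 85% power, and the more than 80% after 5% loss, ignore that only eight schools are randomised; on the stated inputs power is about 71% and 70%

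*Protocol article*

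**What the plan says.** The Protocol article, *Sample size and power*, builds its case on the MHPK-10 score: "With a need for 4 schools per arm with 50 students per school", a two-sided 5% level and 85% power. On clustering, "we assumed a conservative and modest estimate of ICC (ρ) between 0.01 and 0.05", and "the design effect varied from 1.5 to 3.5 for ICC (ρ) values from 0.01 to 0.05, respectively". The resulting detectable difference is 0.37 to 0.56 SD. Two power claims follow: "We expect a minimum sample size of 400 across 8 schools for 85% power", and then "Even with a 5% loss to follow-up, the study will still have more than 80% power".

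The section mentions no t distribution, no degrees of freedom and no allowance for the small number of clusters. *Study design* makes the school the unit of randomisation, and *Plan of analysis* says that the principal analysis will account for clustering by school.

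**The concern.** Multiplying the variance by a design effect allows for students in one school resembling each other. It does not allow for the between-school variance having to be estimated from eight schools. The arms differ only between schools, so the treatment contrast has 8 − 2 = 6 degrees of freedom, however many students or repeated measurements each school contributes. At 6 degrees of freedom the gap between normal and t quantiles is large.

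If the power was computed with normal quantiles, both printed power claims are too high for this design. The practical risk is in reading the result: a null finding on the primary outcome would be taken as coming from an 85%-powered trial when the chance of missing the assumed effect was much larger.

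**Working it through.** **Inputs, all from *Sample size and power*.** Schools per arm k = 4; students per school m = 50, so 200 per arm; ICC 0.01 and 0.05; two-sided α = 0.05; differences d = 0.37 SD (ICC 0.01) and 0.56 SD (ICC 0.05); loss 5%, taken as even across schools (m = 47.5, 190 per arm, all eight schools kept).

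**Step 1: reproduce the plan's figures.**
- Design effect DE = 1 + (m − 1) × ICC: 1 + 49 × 0.01 = 1.49 and 1 + 49 × 0.05 = 3.45. The article prints these as 1.5 and 3.5.
- Standard error of the difference, in SD units: √(2 × 1.49/200) = 0.1221 and √(2 × 3.45/200) = 0.1857.
- Detectable difference with normal quantiles: (1.960 + 1.036) × SE = 0.366 and 0.557. With the rounded design effects it is 0.367 and 0.561. Both round to the printed 0.37 and 0.56.
- Normal-quantile power at 0.37 and 0.56: 85.8% and 85.4%. After 5% loss: 84.6% and 84.9%, consistent with the claim of more than 80%.
- A one-sided test would give about 91% to 92%, which does not fit. A calculation on 6 degrees of freedom gives 0.44 and 0.67, which does not fit either.

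The article does not name its quantiles. That they were normal is an inference, but both ends of the printed range match.

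**Step 2: same inputs, 6 degrees of freedom.** The noncentrality is d/SE, the critical value is t(0.975; 6) = 2.447, and power comes from the noncentral t distribution.

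| Case | DE | SE | d/SE | Power, normal | Power, t(6) | Stated |
|---|---|---|---|---|---|---|
| m = 50, ICC 0.01, d = 0.37 | 1.49 | 0.1221 | 3.031 | 85.8% | 71.5% | 85% |
| m = 50, ICC 0.05, d = 0.56 | 3.45 | 0.1857 | 3.015 | 85.4% | 71.1% | 85% |
| m = 47.5, ICC 0.01, d = 0.37 | 1.465 | 0.1242 | 2.980 | 84.6% | 70.1% | >80% |
| m = 47.5, ICC 0.05, d = 0.56 | 3.325 | 0.1871 | 2.993 | 84.9% | 70.5% | >80% |

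Simulated t-tests on school means (100,000 runs per row) gave 71.8%, 71.2%, 70.2% and 70.4%.

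**Step 3: difference detectable on 6 degrees of freedom.** The noncentrality needed for 85% power is 3.608, so at m = 50 the difference is 3.608 × 0.1221 = 0.44 and 3.608 × 0.1857 = 0.67. After 5% loss it is 3.608 × 0.1242 = 0.448 and 3.608 × 0.1871 = 0.675. Even 80% power before any loss needs 0.41 to 0.63 SD.

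**Step 4: could a 1.96 cut-off rescue the 85%?** A statistic with 6 degrees of freedom exceeds ±1.96 under the null hypothesis with probability 9.8%. Keeping the normal cut-off would therefore nearly double the 5% level that the same section sets. The 85% and the 5% cannot both hold.

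**The case against.** The strongest reply is that 71% is not the settled power of the planned analysis. *Plan of analysis* foresees a linear mixed model with repeated measures and adjustment for confounders, and a baseline score is collected. Suppose baseline enters the model and its correlation with follow-up is r at both student and school level (an assumption). Power on 6 degrees of freedom at 50 per school is then about 75% for r = 0.3, 83% for r = 0.5 and 88% for r = 0.6. With r = 0.5 and 5% loss it is about 82%, which would satisfy the second claim. If the gain is at student level only, r = 0.5 gives 79% (ICC 0.01) and 74% (ICC 0.05). The one figure in the article, a test-retest r of 0.74 under *Primary outcome*, is an imperfect guide to an interval of six weeks or more. The point stands as a limit on what 71% describes. It does not rescue the printed figures: the sample size section credits no such gain, the analysis section does not commit to baseline adjustment, and a school-level covariate would cost a degree of freedom (67.6% to 68.1% at 5, before any gain in precision).

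Three smaller points:
- Given normal quantiles, the paragraph's figures agree with each other. That is so; the fault lies in the reference distribution.
- Each difference is paired with its own ICC. For 0.56 SD, power on 6 degrees of freedom is 97% at ICC 0.01, 91% at 0.02 and 84% at 0.03. That is correct, but the article claims 85% across the whole pairing.
- Calling 400 a minimum can be read as the number required rather than a floor on enrolment. That reading is fair, so the word is only an editorial matter.

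**Conclusion.** The concern holds. On the section's own inputs, power is about 71% rather than 85%, and about 70% rather than more than 80% after 5% loss, at both ends of the ICC range. That is a shortfall of roughly 14 percentage points, and the chance of missing the design effect is about 29% instead of 15%.

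The figures assume a valid 5% test on 6 between-school degrees of freedom, equal school sizes, no baseline adjustment and loss spread evenly with all eight schools retained. The equal-size assumption is favourable, since the article gives 50 only as an average. If sizes varied with a coefficient of variation of 0.3 to 0.5 (an assumption, not in the article), power at a mean of 50 would be about 64% to 70%. The conclusion does not depend on that range.

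**What to change.** Restate *Sample size and power* on a t distribution with 6 degrees of freedom:
- about 71% power for 0.37 SD (ICC 0.01) or 0.56 SD (ICC 0.05) with 50 students per school;
- about 70% after 5% loss;
- a difference detectable with 85% power of 0.44 to 0.67 SD, or 0.448 to 0.675 SD after loss.

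Delete the sentence claiming more than 80% power after loss, and say that the figures assume equal school sizes and no baseline adjustment. If the sponsor wants to rely on baseline adjustment to recover power, the section should say so and give the assumed correlation. It would also be clearer to call 400 the expected enrolment, since 8 × 50 is built on an average and precedes exclusions for consent, assent and baseline absence.

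The cost is one reworded paragraph and a less favourable power statement; no extra schools are needed to make the text correct. If the sponsor prefers to restore the power itself, the same inputs give about 84% with 5 schools per arm (8 degrees of freedom) and 91% to 92% with 6 (10 degrees of freedom), before loss. *Trial status and review* placed recruitment after March 2022, so at the time of the article either course was open before any data were collected.
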